**Figure 2 F2:**
[figure not shown]
Pain diary completed by the patient on a daily basis.

Secondary outcome measures of efficacy are:

• Proportion of failures by week

• Kaplan-Meier analysis of time to failure

• Average change in the pain intensity numerical rating scale PI-NRS by week

• Average change in PI-NRS (best response)

• Median change in the number of paroxysms by week

• Median change in the number of paroxysms (best response)

• Patient and physician global impression of change

• Average change in the Brief Pain Inventory BPI-Facial by week [35]

• Average change in the BPI-Facial (best response)

• Number and severity of paroxysms of pain in the 21-day open-label period, both evoked and spontaneous

• Average 24-h pain intensity numerical rating scale (PI-NRS)

• Patient and Physician Clinical Global Impression of Change

Other measures will include:

• Adverse events, vital signs, ECG and safety laboratory samples will be collected throughout the study

• Adverse event profile: this questionnaire was developed for epilepsy to understand the common AEs associated with epilepsy [36,40], collecting it at screening, day 21 and the last day in the study to try and compare tolerability on CNV1014802 compared to other anti-epileptics they may be taking at screening.

• Medical Outcomes Study-Cognitive Scale (MOS-Cog) will be completed at screening and the end of the study [38,39]

• Assessment of blindedness of study medication: Both the patient and clinician will provide a guess as to which medication (CNV1014802 or placebo) was administered during the double-blind treatment period

• Pre- and post-dose plasma concentrations of CNV1014802

• Presence of genetic mutations in sodium channel (Nav1.1, Nav1.2, Nav1.3, Nav1.6 and Nav1.7) or calcium channel (Cav2.2 and Cav2.1) genes

If the patient requires a drug treatment for their TN pain other than paracetamol, they will be considered a treatment failure, also if they develop any of the following: seizure or suspected seizure, elevated hepatic transaminases, QT prolongation, drug-related rash, and moderate to severe CNS adverse events.

### Inclusion and exclusion criteria

All patients are aged 18 to 80 years of any gender. The main inclusion and exclusion criteria are shown in Table 1; the others are listed on the website http://www.clintrials.gov, trial no. NCT01540630.

**Table 1 T1:** CNV1014802 in patients with trigeminal neuralgia inclusion and exclusion criteria

** *Major inclusion criteria* **	** *Major exclusion criteria* **
A patient will be eligible for inclusion in this study only if all of the following criteria apply:	A patient will not be eligible for inclusion in this study if any of the following criteria apply:
1. The following diagnostic criteria for trigeminal neuralgia must be met:	1. Patients who are known non-responders to sodium channel blockers at therapeutic doses. If patients have previously been unable to tolerate sodium channel blockers and therefore has not been able to take doses within the therapeutic dose range, they may still be included.
Paroxysmal attacks of pain lasting from a fraction of a second to 2 min affecting one or more divisions of the trigeminal nerve	
Pain has at least one of the following characteristics:	
i. Intense, sharp, superficial or stabbing	
ii. Precipitated from trigger areas or by trigger factors	
iii. Attacks are stereotyped in the individual patient	
There is no clinically evident neurological deficit	
Not attributed to another disorder	
2. Frequency criteria for numbers of paroxysms:	2. A positive history of HIV.
Patients must have suffered a minimum of 3 or more paroxysms of pain per day, rated at an intensity of 4 or more on the pain NRS, on at least 4 days during the last 7 days prior to entry into the open-label treatment period.	
3. Male or female between 18 and 80 years of age inclusive at the time of signing the informed consent.	3. A positive pre-study hepatitis B surface antigen or positive hepatitis C antibody result within 3 months of screening.
4. A female patient is eligible to participate if she is of non-childbearing or child-bearing potential and agrees to use one of the contraception methods listed.	4. History of any liver disease within the last 6 months, with the exception of known Gilbert’s disease.
5. Male patients must agree to use one of the contraception methods.	5. History of excessive regular alcohol consumption within 6 months of the study defined as: an average weekly intake of >28 units or average daily intake >4 units for males; an average weekly intake >21 units or average daily intake >3 units for females. One unit is equivalent to 8 g of alcohol: a half-pint (~240 ml) of beer, 1 glass (125 ml) of wine or 1 (25 ml) measure of spirits.
6. Body weight ≥ 50 kg for men and ≥ 45 kg for women.	6. Patients with a history or risk of seizures or a history of epilepsy, head injury or related neurological disorders.
7. BMI ≤34.9.	7. Patients with a history of uncontrolled or poorly controlled hypertension.
8. Capable of giving written informed consent, which includes compliance with the requirements and restrictions listed in the consent form. Informed consent must be obtained prior to the commencement of any study-related procedures.	8. History or presence of significant cardiovascular, gastrointestinal, or renal disease or other condition known to interfere with the absorption, distribution, metabolism or excretion of drugs, which, in the opinion of the investigator, may interfere with the study procedures or compromise patient safety.
	9. Patients with conditions known to affect cardiac conduction or a personal or familial history of Brugada syndrome.
	10. Females of child-bearing potential only: pregnant females as determined by positive urine or serum hCG test at screening or prior to dosing.
	11. Lactating females.
	12. History or presence of any clinically significant abnormality in vital signs/ECG/laboratory tests, or any medical or psychiatric condition, which, in the opinion of the investigator, may interfere with the study procedures or compromise patient safety.
	13. The patient has a history of suicidal ideation and/or suicide attempts.
	14. The patient has clinical evidence of recent major depression (by patient’s medical history).

Patients must have classical trigeminal neuralgia fulfilling all the criteria of the IHS [13]. They must have suffered a minimum of three or more paroxysms of pain per day, rated at an intensity of 4 or more on the pain NRS, on at least 4 days during the last 7 days prior to entry into the open-label treatment period. The following patient categories may be considered for the study: suboptimal responders or intolerant to sodium channel blockers, responders to sodium channel blockers who are willing to be washed out from any sodium channel blockers prior to the run-in period, suboptimal responders to pregabalin or gabapentin, recurrence of trigeminal neuralgia following a remission including (but not limited to) patients who have previously had a positive response to surgery, treatment naïve and on waiting list for surgery.

It is considered useful for all patients to have had some form of imaging done to exclude symptomatic TN and also to have had a dental examination to exclude any potential dental causes. Patients with significant autonomic symptoms or other neuropathic pain are to be excluded.

In view of the fact that CNV1014802 is extensively metabolized, and that the drug interaction potential in humans has not yet been fully evaluated, a variety of drug types have to be stopped prior to study commencement, and approved concomitant medications must have been stable for at least 3 weeks prior to day 0. This includes but is not limited to sodium channel blockers or drugs that adversely interact with a monoamine oxidase-B inhibitor: MAOIs, antidepressants, opioids and sympathomimetic agents. Other than gabapentin and pregablin, no other antiepileptic drug (AED) is allowed.

Among the exclusion criteria are patients who are known non-responders to sodium channel blockers at therapeutic doses and those with a history of uncontrolled or poorly controlled hypertension. Patients with a history or presence of significant cardiovascular, gastrointestinal or renal disease or other condition known to interfere with the absorption, distribution, metabolism or excretion of drugs are also excluded.

The rescue medication is paracetamol only to a maximum dose of 4 g/day.

As the trial is intended to be carried out in multiple countries, it is crucial to ensure that only classical TN patients are recruited and not those whose diagnosis is equivocal and who had tried a large number of drugs with poor response. The data-monitoring committee (DMC) is made up of three clinical investigators with experience in diagnosing patients with TN ([name]), the medical director and study manager from Convergence and from the CRO medical monitor, statistician and project leader. Their remit as well as verifying the diagnosis is to evaluate ongoing efficacy and safety data from the open-label period and to recommend: the dose of CNV1014802 to be used following review of the first ten evaluable subjects completing the open-label period. All patients considered for screening are required to complete a two-page form on diagnostic criteria to be considered by the DMC and approved by at least two of the investigators. The DMC also receives weekly reports on the progress of the trial and numbers required from each center and their progress through the study. It can also terminate the study depending on the efficacy and tolerability of the drug.

All the data from the trial are collected on electronic clinical record forms and anonymized prior to submission, and each site is visited by the project lead and local lead from the CRO. All investigators must adhere to Good Clinical Practice (GCP) and have undergone the appropriate training. All the investigational site staff took part in the protocol training program, either face to face or web based.

The study is double-blind and there are strict restrictions on unblinding. The investigator or treating physician may unblind a patient’s treatment assignment only in the case of an emergency, when knowledge of the study treatment is essential for the appropriate clinical management or welfare of the patient.

Pharmacovigilance staff acting on behalf of the sponsor may unblind the treatment assignment for any patient with a serious adverse event (SAE). If the SAE requires that an expedited regulatory report be sent to one or more regulatory agencies, a copy of the report, identifying the patient’s treatment assignment, may be sent to clinical investigators in accordance with local regulations.

### Power calculation

The aim is to enroll sufficient patients to randomize 30 responders into the double-blind randomized phase of the study. If evaluable data are available from 22 patients entering the randomized phase, assuming a 20% failure rate for CNV1014802 and a 67% failure rate for placebo, 11 evaluable patients per treatment arm (22 in total) would provide 80% power to detect a difference of 47% between the proportion of failures on CNV1014802 and placebo, assuming a one-sided test with a type I error rate of 5%.

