### Randomization and allocation concealment mechanism

In the initial open-label treatment period, all patients will receive CNV1014802.

Patients will be randomized to CNV1014802 or placebo, in a 1:1 ratio, in accordance with the randomization schedule. The randomization schedule will be generated by the CRO using the PROC PLAN procedure of SAS®, a validated computer system. Eligible patients will be randomized into the study on day 21. The randomization schedule will be stratified by whether the patient is on existing pain medication (adjunct) or not (monotherapy). Equal numbers of patient on adjunct and monotherapy are not required.

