### Outcome measures

The primary outcome measure of efficacy is the number of treatment failures on CNV1014802 vs. number of treatment failures on placebo throughout the double-blind treatment period. Patients are classified as a treatment failure if they meet one of the following criteria:

i. A 50% increase in the frequency of paroxysms compared to the final 7 days of the open-label period to more than three paroxysms within a 7-day period

ii. When more than three paroxysms are reported in a 7-day period, a 50% increase in the severity of pain experienced in the paroxysms compared to the final 7 days of the open-label period

iii. A Patient Global Improvement of Change rating of much worse/very much worse

iv. The patient discontinues the study because of ‘lack of efficacy.’

v. The patient discontinues because of an adverse reaction or poor tolerability considered to be related to the study medication

During the double-blind randomized phase, patients will be evaluated to determine whether they meet the failure criteria at each clinic visit, which will occur every 7 days in the double-blind treatment period. The data for the frequency and severity of the pain will be taken from the daily diaries completed by the patients. Figure 2 is an example of such a diary.

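### At 11 evaluable patients per arm, the stated 80% power and the stated one-sided 5% type I error cannot both hold: no test of size at most 5% exceeds about 74% power

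*Protocol article*

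**What the plan says.** The primary outcome (protocol article, Outcome measures) is binary: "the number of treatment failures on CNV1014802 vs. number of treatment failures on placebo throughout the double-blind treatment period". Allocation is equal: "Patients will be randomized to CNV1014802 or placebo, in a 1:1 ratio" (Randomization and allocation concealment mechanism).

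The Power calculation section first sets the recruitment target: "The aim is to enroll sufficient patients to randomize 30 responders into the double-blind randomized phase of the study". It then makes its power statement for a smaller number: "If evaluable data are available from 22 patients entering the randomized phase", and "assuming a 20% failure rate for CNV1014802 and a 67% failure rate for placebo", it says that "11 evaluable patients per treatment arm (22 in total) would provide 80% power to detect a difference of 47" percentage points, "assuming a one-sided test with a type I error rate of 5" per cent. Neither a test nor a formula is named. The Discussion calls the study small and says it should be regarded as a pilot.

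**The concern.** With 11 patients per arm, the expected number of failures on active drug is 0.20 × 11 = 2.2. Normal-approximation formulas are unreliable at such counts, and the choice among them moves the answer by several points. All inputs are given and the endpoint is a count in each arm, so the stated power can be checked exactly.

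If the 80% comes only from an approximation, one of two things is true at 22 evaluable patients. Either a test that keeps its 5% level has less power than stated, or the test with about 80% power has a true error rate above 5%. In the first case a null result would be judged against a power that this sample does not have. In the second, the false-positive risk rises on a level that is already one-sided 5%.

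**Working it through.** **Inputs** (Power calculation section): failure rates 0.20 (active) and 0.67 (placebo), difference 0.47; 11 evaluable per arm; one-sided 5%, z = 1.645; 80% power, z = 0.842.

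**Step 1. Reproduce the stated figure (unpooled normal formula).**
- Variance term: 0.20 × 0.80 + 0.67 × 0.33 = 0.1600 + 0.2211 = 0.3811.
- n per arm = (1.645 + 0.842)² × 0.3811 / 0.47² = 10.67, rounded up to 11.
- Power at 11: 0.47 / √(0.3811/11) = 0.47 / 0.1861 = 2.525; 2.525 − 1.645 = 0.880; Φ(0.880) = 81.1%.

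This matches the plan's 11 per arm and 80%.

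**Step 2. Other normal formulas at 11 per arm.**
- Pooled variance under the null: mean rate 0.435, √(2 × 0.435 × 0.565 / 11) = 0.2114. Power = Φ((0.47 − 1.645 × 0.2114) / 0.1861) = Φ(0.657) = 74.4%. This formula needs 13 per arm for 80%.
- Arcsine: 75.1%.
- Pooled with continuity correction: 56.7%, needing 17 per arm.

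**Step 3. Exact power and true size at 11 per arm.** Let X and Y be the failures on active drug and placebo, each 0 to 11, so there are 12 × 12 = 144 possible outcomes. For a test with rejection region R:
- Power = Σ over R of Bin(x; 11, 0.20) × Bin(y; 11, 0.67).
- True size = the maximum over a common failure rate p of Σ over R of Bin(x; 11, p) × Bin(y; 11, p).

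| Test, one-sided nominal 5% | Power | True size (maximum) |
|---|---|---|
| Uncorrected z (chi-square) | 79.7% | 6.7% |
| Fisher exact | 64.3% | 2.6% |
| Fisher mid-p | 66% | 3.4% |
| Barnard-type with z statistic | 66.3% | 4.5% |
| Boschloo | 71.7% | 4.7% |

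One outcome shows where the difference arises. With 3 failures of 11 on active drug and 7 of 11 on placebo, the pooled rate is 10/22 and z = (4/11) / √(2 × (10/22) × (12/22) / 11) = 0.3636 / 0.2123 = 1.71. This exceeds 1.645, so the z-test rejects. The one-sided Fisher p-value is (11 + 605 + 9,075 + 54,450) / 646,646 = 0.099. Neither Fisher nor Boschloo rejects there.

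**Step 4. Best possible power at size 5%.** Power was maximised over all rejection regions, subject to size at most 5% over a fine grid of common failure rates. The maximum is 73.9% for a non-randomised test and 74.1% if randomised tests are allowed. The conflict at 11 per arm therefore does not depend on which test is used.

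**Step 5. Larger evaluable numbers, same rates.**

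| Evaluable per arm | Fisher power | Boschloo power | Boschloo true size |
|---|---|---|---|
| 11 | 64.3% | 71.7% | 4.7% |
| 13 | 67.2% | 77.5% | 3.8% |
| 14 | 69.5% | 82.0% | 4.4% |
| 15 (all 30) | 75.0% | 85.7% | 4.95% |
| 16 | 79.8% | 85.3% | 4.3% |

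Mid-p has true size 4.95% at 15 per arm but 5.5% at 16, so it does not guarantee the level at every sample size.

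**The case against.** **The figure is not a miscalculation.** A reader might infer an arithmetic slip. The document does not support that: a standard formula returns 11 per arm, and a standard test has 79.7% exact power there. This objection stands. The fault is a large-sample method applied to a very small sample.

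**The test is not named, and that is usually left to the analysis plan.** With an uncorrected chi-square test, power is about 80% and the only defect is excess size: 4.9% if the common failure rate is 20%, 5.8% at 67% and at most 6.7% at 50%. Some analysts accept a nominal level of this kind. The silence about the test is indeed no finding. It does not rescue the sentence, though, because the 74.1% ceiling applies to any test whose true size is at most 5%.

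**The 22 patients are a reduced-data case.** A reader might infer that the whole trial falls short of 80%, or that it needs more patients. The document does not support either. It plans to randomize 30, and at 15 per arm Boschloo gives 85.7% at size 4.95%. This objection stands and limits the point to the 22-patient statement. It is not a full answer, since the section allows for 30 − 22 = 8 non-evaluable patients and Fisher gives only 75.0% even at 15 per arm.

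**It is a pilot with uncertain assumptions.** The Discussion says so and admits that the expected change is hard to determine. That lowers the consequence, but it does not make the stated combination correct.

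**Conclusion.** The point holds for the case of 22 evaluable patients. At 11 per arm, with 20% versus 67% failures, 80% power and a true one-sided type I error of 5% are incompatible. The usual tests that hold 5% give 64% (Fisher) to 72% (Boschloo), with a ceiling of about 74% for any such test. A true 47-point difference would be missed about 28% (Boschloo) to 36% (Fisher) of the time, against the 20% implied. Alternatively, the test with about 80% power has a true error rate of up to 6.7%.

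This rests on the plan's own failure rates, equal evaluable numbers per arm, an unstratified comparison of two proportions, and reading the 5% as the true error rate. It should be fixed, but it is not critical: the planned 30 can restore 80% with an exact unconditional test, and the study is presented as a pilot.

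**What to change.** In the Power calculation section:

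1. Replace the 80% for 22 evaluable patients with about 64% (Fisher) or 72% (Boschloo), one-sided 5%.
2. Add that 80% is reached from 14 evaluable patients per arm with Boschloo (82%), and that if all 30 randomized patients are analysed the power is 75% (Fisher) or 86% (Boschloo, true size 4.95%).
3. State which size-controlling test each figure refers to. If mid-p is preferred, check its true size at the numbers actually analysed.

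The cost is a reworded paragraph and a less favourable figure for the 22-patient case. Enrolment, allocation and endpoint stay as they are.

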## Discussion

This is the first time that such a design has been used to evaluate a drug for TN. It is also the first time that a drug is being used that has not first been evaluated in epilepsy. Its design conforms with the CONSORT guidelines, which have been shown to improve the quality of trial reporting [41], and although conceived before the statement on defining the standard protocol for clinical trials was published, it does conform to these [26]. Drug trials in TN are rare, heterogeneous and often contain serious methodological issues. Only 11 randomized placebo controlled trials on classical TN have been conducted since 1967. These trials recruited very different patient numbers (ranging from 3 to 77 participants), often embedding TN patients into a broader facial pain patient spectrum study to gain more statistical power. Formal power calculations were generally not provided in most previous TN trials. The study by Gilron et al. [42] is an extreme example of recruitment difficulties that all TN trials face. This placebo-controlled, multiple cross-over pilot study included only three patients. The present study is also small and needs to be regarded as a pilot, which will enable more accurate power calculations to be performed in the future. The primary outcome measure chosen is pain relief as is the norm for pain trials, yet it may be that other outcomes such as improved quality of life due to reduced side effects may be of greater importance. Many patients report that the “odd twinge” does not significantly impact on their lives, but tiredness, impaired cognitive function and ataxia from the high-dose medication has a significant impact on activities of daily living.

Most centers specialized in the treatment of patients with TN do not have a large enough patient base of the right type of patients including those willing to have their medication regimens changed.

A variety of strategies has been suggested to increase recruitment to trials of both participants and clinicians, and a recent systematic review suggests increased education of clinicians about the benefits of RCTs is needed [43]. Thus, the sites chosen have a special interest in TN with experienced clinicians, and it is hoped they will be able to recruit the appropriate patients. It takes time to recruit patients to clinical trials, and there are few data available on this topic. A recent study of an orthodontics multicenter RCT showed that it took on average 19 min to recruit a patient to the study and then a further 110 min per patient to fully recruit to the study and ensure all administrative data were available [44]. The variations between the centers were large in respect to the administrative data time as it often depended on the research support staff that was available. There was also considerable time involved in meetings of the principal investigators, and the authors suggest that these timings are potentially much higher in more complex studies.

To improve recruitment to this trial ethics approved data for patients were prepared and distributed to clinicians attending relevant conferences and for placement in a Trigeminal Neuralgia Support group newsletter in the UK. Recruitment of patients could be problematical for other reasons that are specific to this condition. TN causes very severe pain, and once stabilized on medications patients are often reluctant to change for fear their pain will return or become unmanageable. They may have used a range of other AEDs including the two permitted ones in the past and so be reluctant to go back to them. Currently the most effective AEDs cannot be used. Patients with classical TN who have neurovascular compression of the nerve (seen on MRI) may opt to have an operation rather than try further medications as the outcomes from surgery can be better [15]. The population most at risk is the elderly, and they are likely to have medical conditions that preclude their inclusion in the trial.

Different disease definitions as well as imprecise allocation of non-standardized diagnostic criteria make comparison of the different patient populations virtually impossible. Many trials do not refer to any particular diagnostic criteria at all but are content to describe their patient as having classical TN without further clarification or definition of that term. This study uses the international classification of headache disorders (ICHD-3beta) and an experienced data management committee to ensure a standardized patient selection and prevent non-classical TN patients entering the trial.

Incomplete or insufficiently defined outcome parameters, which were not clearly stated in many of the RCTs conducted until now, is another serious problem. Many trials failed to report dropouts or withdrawals, while those that did report these measures did not use intention-to-treat analysis to analyze their study results. This is particularly problematic since the dropout and withdrawal rates in most TN trials are very high. Information on demographics and clinical characteristics of the different treatment groups is often incomplete and lacks a clear comparison of baseline data with regard to gender, age, duration of disease and pain scores.

Allocation concealment and blinding are often problematic in randomized controlled trials on TN. Often blinding methods are not reported in detail, so that it remains unknown who was blinded to what. All of these trials stated that they were randomized, but most did not describe the utilized method of randomization or whether the randomization method used was effective in regard to homogenizing the groups that were to be compared in the final analysis.

Selective reporting is generally considered a minor problem in these small and often confined studies. Some studies however did not clearly state what assessment tools they used for their analysis, while others did not report the adverse events or side effects of the study drug consistently. The possibility of patients going into spontaneous remission with treatment or without was not raised by most authors when interpreting their data.

Other potential sources of bias were often underreported. Many studies use the investigated drug as add-on to carbamazepine or other established treatment regimens [34,43,45-49]. Considering the pharmacologic profile of carbamazepine and other frequently used antiepileptic drugs with many drug interactions and hepatic metabolism, this may also pose serious consequences to the trial outcome and data interpretation of these trials that we are only starting to marginally comprehend. One of the largest RCTs comparing carbamazepine and oxcarbazepine in 46 patients has only been reported as a conference abstract, and the other study, possibly the same one in a German journal, included 48 patients [50]. The EERW design is new, and there will be few trials against which to compare the results, but the outcome measures being used are from the range of those suggested by Dworkin et al. [33]. The recently extended Brief Pain Inventory [35] has been psychometrically tested but has not yet been tested in terms of sensitivity to change; however, the first section has been used in extensive analgesic trials and so outcomes can be compared.

This protocol is being published prior to the study being completed in accordance with the recent literature [51] so that it will be possible to compare what was intended and what was actually done, and it has been registered on a trials register since February 2012, which may help to recruit patients. A comparison of registered and published primary outcome measures in RCTs shows selective outcome reporting is still prevalent [52], but this may also be due to an incorrect choice of outcome measures. In this study it is difficult to determine how large a change can be expected as there are currently so few data in the RCTs on TN, and unlike other pain trials, 100% pain relief can be achieved as opposed to the usual 50%.

The results of the trial will be published and presented at conferences including those for patients.

